# Impact of non-muscle cutting periumbilical transverse incision on the risk of incisional hernia as compared to midline incision during laparoscopic colon cancer surgery: a study protocol for a multi-centre randomised controlled trial

**DOI:** 10.1186/s13063-023-07162-x

**Published:** 2023-02-28

**Keywords:** Laparoscopes, Incisional hernia, Laparotomy, Wounds and injuries, RCT, Protocol

## Abstract

**Background:**

Minimally invasive surgery has become popular as a surgical approach for colorectal cancer because it has fewer complications related to the abdominal incision and perioperative complications. However, the incidence of incisional hernias in laparoscopic surgery has been reported to be similar to that in open surgery. We developed a new method, the non-muscle-cutting periumbilical transverse incision, for a small incision in laparoscopic colon cancer surgery. This study aims to evaluate the effectiveness of the non-muscle-cutting periumbilical transverse incision in comparison with the midline incision in reducing the incidence of an incisional hernia in patients undergoing laparoscopic colon cancer surgery.

**Methods:**

This is an open-label, multi-centre, parallel, superiority, and randomised trial. Altogether, 174 patients will be allocated in a 1:1 ratio to either the midline incision or the non-muscle-cutting periumbilical transverse incision group, after stratifying by the location of the tumour (right- or left-sided). The primary outcome of this study is the incidence of incisional hernias (both symptomatic and radiologic hernias) at 12 months after surgery. The secondary outcomes include operative outcomes, 30-day postoperative complications, pathological results, and patient-reported outcomes (short form-12 health survey questionnaire and body image questionnaire). Both primary (intention-to-treat) and secondary (as-treated principles) analyses will be performed for all outcomes. The statistical significance level was set at *p* < 0.05 (two-sided testing).

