### Sample size estimation

This study aimed to test the superiority of the non-muscle-cutting periumbilical transverse incision over the midline incision, and the sample size was estimated based on the primary outcome (the incidence of incisional hernia at 12 months after surgery). Our previous retrospective study showed that the incidence of incisional hernias was 2.4% and 14.9% in non-muscle-cutting periumbilical transverse and midline incisions, respectively [6]. For this study, a conservative estimate rounded these incidences up to 2.5% and 15%, respectively. The sample size calculations were conducted in R using the pwr (pwr.2p.test); the required sample size for a superiority trial was determined to be 158 patients using power analysis (power = 85%, *ɑ* = 0.05, two-sided), and the dropout rate was anticipated at 10%. Finally, a total of 176 patients are required for randomisation.

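### The abstract plans to randomise 174 patients and the sample-size section 176; only 176 follows from the protocol's own inputs

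*Protocol article*

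**What the plan says.** The Methods paragraph of the abstract states: "Altogether, 174 patients will be allocated in a 1:1 ratio". The section on sample size estimation ends: "Finally, a total of 176 patients are required for randomisation".

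The same section shows how its figure was reached. The retrospective study behind the assumptions is reported thus: "the incidence of incisional hernias was 2.4% and 14.9% in non-muscle-cutting periumbilical transverse and midline incisions, respectively". For the trial, "a conservative estimate rounded these incidences up to 2.5% and 15%, respectively". From these rates "the required sample size for a superiority trial was determined to be 158 patients", with power 85% and a two-sided 5% level, using the two-proportion function of the R pwr package. For losses, "the dropout rate was anticipated at 10" per cent. The abstract confirms the two-sided 5% level.

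**The concern.** Both sentences describe the total number randomised, so they cannot both be right. It is not a case of one figure counting patients enrolled and the other patients evaluable: the evaluable number is given separately as 158. Both sentences are current text, and no other section explains the difference.

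A planned sample size is a figure that readers and later reviewers use to compare planned with actual enrolment. With two published totals, a trial that closes at 174 could look short, and one that closes at 176 could look over-recruited. The section on trial status does not settle the matter. It says when the maximum enrolment is expected but gives no number. The questions are which total the stated inputs support, and whether the difference matters for power.

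**Working it through.** **Inputs**, all from the section on sample size estimation unless noted:

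- hernia incidence at 12 months: 2.5% (transverse) and 15% (midline)
- power 85%
- two-sided alpha 0.05 (also in the abstract)
- 1:1 allocation (abstract; section on randomisation)
- dropout 10%
- method: the pwr two-proportion routine, which works with the arcsine effect size h

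**Step 1. Reproduce the 158.**

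h = 2·arcsin(√0.15) − 2·arcsin(√0.025) = 0.7954 − 0.3176 = 0.4778

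n per arm = 2 × ((1.960 + 1.036) / 0.4778)² = 78.64, rounded up to 79

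Total = 2 × 79 = 158. This matches the protocol exactly. Other common formulas do not give 158: pooled variance gives 91 per arm, unpooled variance 88, and the continuity-corrected version 106. The arcsine formula is the one the protocol's software uses.

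**Step 2. Reproduce the 176.**

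N randomised = 158 / (1 − 0.10) = 175.6, rounded up to 176, or 88 per arm. This also matches exactly.

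**Step 3. Test each total against the 158 required.**

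| Randomised | Evaluable after 10% dropout | Per arm | Against 158 |
|---|---|---|---|
| 174 | 174 × 0.90 = 156.6 | 78.3 | 1.4 short |
| 176 | 176 × 0.90 = 158.4 | 79.2 | met |

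**Step 4. Power at each total**, as Φ(h·√(n/2) − 1.960):

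- n = 78.3 per arm (174 randomised): 84.8%
- n = 79 per arm (the required 158): 85.2%
- n = 79.2 per arm (176 randomised): 85.2%

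The difference is 0.3 to 0.4 percentage points. An exact calculation for the uncorrected chi-square test agrees: 84.7% with 78 per arm and 85.2% with 79 per arm.

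**Step 5. Where 174 could come from.** The document does not say. Two routes from its own figures reach it:

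- multiplying instead of dividing: 158 × 1.10 = 173.8, rounded up to 174
- using the unrounded rates 2.4% and 14.9%: h = 0.4815, n = 77.45, so 78 per arm and 156 in total; 156 / 0.90 = 173.3, rounded up to 174

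A typing slip is a third possibility. Neither arithmetic route makes 174 the right total under the stated plan. The first leaves fewer than 158 after the stated dropout, and the second uses rates that the section says were replaced by the rounded ones.

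**The case against.** The best defence is that the abstract is only a summary. The one place that shows a calculation does it correctly and ends at 176, and that is the operative statement. This stands: the derivation contains no error, and the defect lies in the abstract's figure.

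The defence can also say that the shortfall has no practical weight, and this stands too. The 10% dropout is a round forecast, and one or two losses more or fewer would move the evaluable number by as much as the whole gap. The section on withdrawal says that patients who withdraw consent between randomisation and surgery are replaced, so the evaluable count is not fixed by the randomised total alone. The limitations paragraph of the discussion already concedes that the sample size may be too small or too large, because it rests on retrospective data.

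Three stronger readings are tempting, and the documents do not support them:

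- A reader might infer that the trial is underpowered. A change of 0.3 to 0.4 points does not support that.
- A reader might infer that the sponsor inflated for dropout in the wrong way. That is one possible origin of 174, but the unrounded rates with a correct inflation give the same number, and the sample-size section inflates correctly.
- A reader might infer that recruitment will stop at 174. No section says so.

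What the defence cannot remove is that two different totals are published for one quantity. The brevity of an article does not explain this, since nothing has been left out: two figures are stated and they disagree.

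**Conclusion.** The point holds as a minor correction. The abstract's 174 and the sample-size section's 176 contradict each other, and 176 is the total that follows from the protocol's stated inputs. The size is two patients randomised, 1.4 evaluable patients short of the 158 required, and about 84.8% power instead of 85.2%. No estimate, test or conclusion of the trial would change.

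The verdict takes the incidences of 2.5% and 15%, the arcsine method and the 10% dropout as the protocol states them. It does not judge whether those assumptions are realistic. It makes no claim about how 174 arose or about the number at which recruitment will actually close.

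**What to change.** Change the abstract to 176 patients (88 per arm) and state that one total throughout. In the sample-size section, one added clause would make the derivation explicit: 158 / (1 − 0.10) = 175.6, rounded up to 176. It would be sensible to confirm that the recruitment target in use is the same number.

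The cost is the correction of one figure, with no change to design or analysis. If the sites happen to be working to 174, the cost is at most two further patients.

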**Discussion:**

This trial may show that the non-muscle-cutting periumbilical transverse incision will reduce the incidence of incisional hernias compared to the midline incision.

**Trial registration:**

Clinical Research Information Service (CRiS) of Republic of Korea, KCT0006082. Registered on April 12, 2021.

## Background

Over the last three decades, clinical trials have shown that minimally invasive surgery is safe for patients with cancer. It has now become a popular surgical approach to treating colorectal cancer [1]. Minimally invasive surgery is less invasive than open surgery, which has a shorter postoperative recovery period and fewer complications related to a long abdominal incision. Most minimally invasive surgical procedures for colorectal cancer can be performed with a few 5–12 mm incisions for trocars, and a small incision is mostly used for specimen extraction. The length of the small incision is significantly shorter than that in open surgery. But it still has wound-related complications, and incisional hernias are one of the most common ones.

Incisional hernias deteriorate cosmesis and quality of life, increase the risk of bowel incarceration and reoperation, and result in additional medical costs. Even though the incidence of incisional hernias in laparoscopic surgery can be expected to be lower than that of open surgery, it has been reported to be similar to that in open surgery [2]. A literature review analysed 43 studies on laparoscopic colorectal resection and reported that the midline incision was the most commonly used approach for specimen extraction, followed by transverse and Pfannenstiel incisions [3]. The incidence of incisional hernia following the small incision was significantly higher following the midline incision than following the Pfannenstiel or transverse incisions. However, in prospective randomised controlled trials, the effectiveness of transverse incision in reducing the incidence of incisional hernia has not been proven [4]. There were no differences in pain scores or the incidence of incisional hernia between the two groups in a randomised controlled trial comparing the vertical periumbilical midline incision and the transverse left iliac fossa incision in laparoscopic anterior resection [5]. In another randomised controlled trial, a transverse incision was made outside of the linea semilunaris and rectus sheath. An intention-to-treat (ITT) analysis showed that the incidence of incisional hernia was similar in both groups [4], but the per-protocol analysis showed that it was significantly higher in the midline incision group. In this study, the failure of the primary outcome in the ITT analysis was because the protocol was violated in the transverse incision group. After all, the transverse incision is less versatile for either hand-assisted or open conversion.

Previous studies placed small transverse incisions for laparoscopic colon cancer surgery outside of the umbilicus, such as the iliac fossa incision or Pfannenstiel incision. We developed a non-muscle-cutting periumbilical transverse incision that is flexible to extract specimens of colorectal cancer and create extracorporeal ileocolic or colocolic anastomoses [6]. We hypothesised that this new transverse incision has benefits in terms of reducing the incidence of incisional hernia, as suggested by previous studies, while overcoming the cosmetic drawbacks of the standard transverse incision.

The current randomised controlled trial compares the incidence of incisional hernia between the midline and non-muscle-cutting periumbilical transverse incisions at 12 months after laparoscopic colon cancer surgery.

## Methods and analysis

### Study design

This multi-centre, open-label, parallel, superiority, randomised trial will compare the effectiveness of non-muscle-cutting periumbilical transverse incision versus midline incision on the incidence of incisional hernia in patients undergoing laparoscopic colon cancer surgery in the Republic of Korea at the following four tertiary hospitals: the Chonnam National University Hwasun Hospital, the Kyungpook National University Chilgok Hospital, the Jeonbuk National University Hospital, and the Pusan National University Yangsan Hospital. The study flow of the assessment, intervention, and follow-up is shown in Fig. 1.

**Fig. 1 Fig1:**
[figure not shown]
Flow diagram of the study protocol. SF-12, short form-12 health survey questionnaire

### Participants

Eligible individuals are identified by the usual clinical team on a list of planned elective surgeries by reviewing patient information in the hospital’s electronic medical records at each institution. When eligibility is confirmed, surgeons will contact patients to provide details of the study background and process and request their participation in the study. Before the study protocol is initiated, each patient will be asked to provide written informed consent after the clinical investigator has explained the nature, significance, and scope of the clinical study appropriately and understandably (both orally and in writing). Clinical investigators are specifically trained medical doctors on the local study team. We began recruiting on April 20, 2021, and anticipate its conclusion in February 2024.

### Inclusion and exclusion criteria

Patients scheduled for elective laparoscopic colon cancer surgery at participating institutions are eligible if they meet the following inclusion criteria: (i) age ≥ 20 years; (ii) presence of pathologically confirmed colon cancer (adenocarcinoma, mucinous carcinoma, or signet ring cell carcinoma); and (iii) ability to understand verbal explanations, read instruction documents, and sign informed consent forms.

Patients meeting at least one of the following criteria are ineligible and were excluded from this trial: planned open surgery; expected incision length of < 1 or ≥ 10 cm; rectal cancer (lower border of tumour located within ≥ 15 cm from the anal verge); planned small incision outside of the umbilical area; palliative surgery for stage IV tumours; planned protective or permanent diversion; emergent surgery; current unhealed wound, fracture, peptic ulcer, or intraabdominal abscess; history of incisional hernia; and participation in any other interventional clinical trial within 6 months.

### Randomisation

Participant screening will be done by the surgeon and confirmed by the research coordinator of each institution. If potential participants meet all protocol eligibility protocol and agree to the informed consent forms, the investigators will enrol the participants and call the research coordinator of the initiating institution (Chonnam National University Hwasun Hospital) the day before the surgery and inform them of which group the registered patient is assigned to. In-hospital patients will be preoperatively allocated in a 1:1 ratio to either the midline or non-muscle-cutting periumbilical transverse incision groups, after stratifying by the location of the tumour (right-sided: caecum-transverse colon; left-sided: descending-rectosigmoid colon), according to the random sequence generated by a web-based randomisation system. The randomisation sequence will be generated independently by the designated staff not involved in outcome data collection and analysis before being provided to the randomisation contract for onward use. A unique study identification number will be assigned to the patients during data collection and analysis to ensure anonymityThe allocation information will also be blinded to the data analyst, and it will remain blinded to the public until a final comparison is performed.

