### Blinding

The surgery team will not be blinded because the small incisions made during the surgery will be different in each case. Patients will also not be blinded, as the incisions will be visible during postoperative wound care. To reduce the bias associated with data collection, the outcome assessor will be separate from the surgery team and blinded to the allocation.

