### Withdrawal of patients

The participants are free to discontinue their participation at any time for any reason without any consequences. If a participant meets newly established or previously unrecognised exclusion criteria or has an urgent medical condition that disqualifies them from participating, the investigator may opt to remove them from the research. Patients who withdraw their consent after randomisation but before surgery will be replaced, whereas those who withdraw their consent after surgery will not be replaced. The data from these patients will not be included in the analysis.

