### Data management and control

Participants’ identities will be kept private by using a research identification number that cannot be linked to their identities. Each centre will keep all patient-identifiable information in the file, apart from the data needed for analysis. To ensure consistent assessment, researchers will be uniformly trained. The result assessor at each centre will first input data into a registered paper-based case report form before entering it into the predesigned electronic version of the case report form. Both the paper and electronic versions of the case report forms will be maintained in a safe location, with only the members of the research team having access to them. All records will be stored for inspection at any time during and for 3 years after the completion of the study report. The study will be monitored by a committee of the Chonnam National University Hwasun Hospital.

Day-to-day support will be provided by the principal investigator (like supervision of the trial, recruitment, and medical responsibility of the patients) and the research coordinator (including data collection and follow-up of the patients) of each participating institution. The principal investigator and research coordinator will meet weekly. The Trial Steering Committee (TSC) will consist of representatives from participating institutions, which will act as a decision-making committee and be responsible for the scientific conduct of the study. The TSC will meet every 3 months, ensure that the trial is conducted following relevant principles, and provide overall supervision.

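### Allocation is known the day before open-label surgery, via a lead-centre coordinator who also has follow-up duties, and patients who withdraw consent before the operation are replaced and left out despite the ITT definition

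*Protocol article*

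**What the plan says.** All references are to the protocol article.

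- **Randomisation, order of steps.** "Participant screening will be done by the surgeon and confirmed by the research coordinator of each institution". After consent, the investigators enrol the patient and "call the research coordinator of the initiating institution", "the day before the surgery and inform them of which group the registered patient is assigned to". The sentence does not make clear who informs whom. The sequence comes from a web-based system and is generated by staff who take no part in outcome data collection or analysis.
- **Data management and control.** Day-to-day support comes from the principal investigator and "the research coordinator (including data collection and follow-up of the patients) of each participating institution". The same section assigns form completion to someone under another title: "The result assessor at each centre will first input data into a registered paper-based case report form".
- **Blinding.** The surgical team and the patients are not blinded, but "the outcome assessor will be separate from the surgery team and blinded to the allocation".
- **Withdrawal of patients.** "Patients who withdraw their consent after randomisation but before surgery will be replaced". Patients who withdraw after surgery are not replaced. A closing sentence leaves the data of withdrawn patients out of the analysis. The investigator may also remove a patient who turns out to meet an exclusion criterion not recognised before.
- **Statistical analysis.** The ITT set, which is primary, is everyone randomised, whichever incision was received.

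**The concern.** Randomisation makes the arms comparable only if patients cannot leave the comparison for reasons linked to their group. Here the group is known a day before an operation performed by a team that is not blinded, and the rules allow a patient who withdraws consent in that interval to be replaced and omitted. If such withdrawals were more frequent, or of a different kind, in one arm, the arms analysed would no longer be those that were randomised.

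The second strand is who handles the allocation. Generation of the sequence is kept apart from outcome data collection, but its release is not: it passes through a coordinator whose role includes data collection and follow-up. Under Outcomes, a hernia can count on the patient interview alone, and a hernia without symptoms needs a positive physical examination as well as CT. Parts of the primary endpoint therefore depend on judgement, and it matters that whoever collects them does not know the group.

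**Working it through.** **1. Who learns the allocation, and when.** On the literal reading of the Randomisation sentence, the investigators tell the coordinator the group; on the likelier reading, the coordinator tells them. On both, the two parties to the call know it the day before surgery. The lead-centre coordinator thus learns it for patients from all four hospitals. I assume that the investigators share it with the operating team, which the Blinding section says is not blinded.

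**2. How far the roles overlap.**

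| Task | Lead-centre coordinator | Coordinators at the other three centres |
|---|---|---|
| Confirms eligibility locally | yes | yes |
| Takes part in the allocation call | yes | not stated |
| Local data collection and follow-up | yes | yes |
| Is the blinded outcome assessor | not stated | not stated |

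Only at the lead centre does the text put the call and the data duties in one role. The Blinding section separates the assessor from the surgical team and is silent on the coordinator.

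**3. The interval between allocation and surgery.** Set side by side, the two rules do not agree:

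- Withdrawal of patients: consent withdrawn after randomisation and before surgery leads to replacement, with the data left out.
- Statistical analysis: ITT contains all randomised patients.

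A patient in this interval is in the ITT set by the second rule and out of it by the first. If the closing exclusion sentence were read as covering only withdrawals after surgery, it would still remove randomised patients from the analysis, so the conflict remains.

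**4. Scale.** The plan's own sample size reproduces with the arcsine method:

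- h = 2·asin(√0.15) − 2·asin(√0.025) = 0.478
- n per arm = 2·((1.960 + 1.036)/0.478)² = 78.6, rounded up to 79, so 158 in total
- 158/(1 − 0.10) = 175.6, rounded up to 176

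The 10% dropout allowance is 176 − 158 = 18 patients and is not split by timing, so it gives no rate for the interval before surgery. Purely as an assumption, 2% to 5% of 176 is 3.5 to 8.8, or about 4 to 9 patients.

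Expected events at the planned rates are 79 × 0.15 + 79 × 0.025 = 11.85 + 1.98 = 13.8, about 14. With χ² = N(ad − bc)²/(product of the four margins) and 79 per arm:

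- 12 v 4 hernias: 158 × (12×75 − 4×67)²/(79×79×16×142) = 4.45, p = 0.035
- 11 v 4 hernias: 158 × (11×75 − 4×68)²/(79×79×15×143) = 3.61, p = 0.057

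One case can move the result across 0.05. This shows that a trial with about 14 events is fragile to any disturbance. It does not measure bias from this source, and neither its direction nor its size follows from the documents.

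**The case against.** The case against is substantial, and several stronger readings fall to it.

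- **A breach of blinded assessment.** A reader might infer that the coordinator's data duties contradict the Blinding section. The article promises blinding for the outcome assessor and the data analyst, not for coordinators. It names a separate result assessor who fills in the forms and nowhere says that the coordinator interviews, examines or reads scans. A breach is not shown.
- **Overlap throughout the trial.** Every centre's coordinator has data duties, but the call goes to one of them. Unblinding through this route is shown for the lead centre only.
- **Failed concealment.** Eligibility, consent and enrolment are listed before the call, and the sequence is generated independently. Nothing shows that allocation is known before enrolment.
- **Patients leaving because of their group.** The article does not say that patients are told before surgery; it explains their lack of blinding by postoperative wound care. The window is clearest for investigators and the surgical team.
- **Limited gain for assessment.** Anyone examining the abdomen may see the direction of the scar, so a cleaner relay would not by itself secure blinded examination.
- **Condensed text.** The full protocol may say more about delegation of duties.

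All of this stands and limits the point. It is also true that randomising the day before elective surgery is not an error in itself. What it does not answer is the combination that the article does state: a group known a day ahead, an unblinded team, and a rule that replaces and omits patients who withdraw consent in between, set against an ITT set of all randomised patients. That is a contradiction between two stated rules, not a detail left to a fuller document.

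**Conclusion.** The point holds in limited form. The main weakness is the interval between allocation and surgery. The procedures as written allow selection after allocation and contradict the plan's own definition of its primary analysis set. The coordinator's overlapping duties at the lead centre are a lesser, avoidable weakness that the article leaves unaddressed.

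The size of any bias cannot be calculated: no withdrawal rate is given, and 4 to 9 patients rests on an assumed 2 to 5%. The conclusion also assumes that the group reaches the surgical team once the call is made. It does not require that patients know their group or that the coordinator assesses outcomes. The change is worth making because it is cheap and, with about 14 events expected, there is little margin for patients dropped after allocation.

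**What to change.** 1. Have the web-based system release the allocation directly to the operating surgeon as late as practicable, for example in theatre before the extraction incision. This looks workable because both groups extend the periumbilical camera port. If the port itself is placed differently by group, which the article does not say, release has to come before the port.
2. State that no coordinator with data-collection or follow-up duties receives or transmits allocations, including at the lead centre, and that the outcome assessor is separate from the coordinator.
3. Reconcile Withdrawal of patients with Statistical analysis, so that patients who leave after allocation stay in the ITT set as far as their consent allows. Extra patients may be recruited to restore numbers, but not as substitutes for those who left. Report departures between allocation and surgery by arm, with reasons, including any that have already occurred.

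Cost: a short amendment and a change of procedure, with no added staff. The surgeon needs system access in theatre and can no longer plan the incision the day before. Because recruitment is open, items 1 and 2 protect only patients still to be enrolled, though separating the assessor from the coordinator also helps follow-up visits still to come. Item 3 can apply to every patient randomised.
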